## Abstract

**Background:**

Weight gain and obesity are common after kidney transplantation, particularly during the first year. Obesity is a risk factor for the development of new-onset diabetes after transplantation, and is associated with reduced graft survival. There is a lack of evidence for effective interventions to prevent weight gain after kidney transplantation.

**Methods/Design:**

The effect of **INTE**nsive **N**utrition interventions on weight gain after kidney **T**ransplantation (INTENT) trial is a single-blind (outcomes assessor), randomised controlled trial to assess the effect of intensive nutrition interventions, including exercise advice, on weight gain and metabolic parameters in the first year after transplantation. Participants will be randomised during the first post-transplant month to either standard care (four visits with a renal dietitian over twelve months) or intensive nutrition intervention (eight visits with a renal dietitian over the first six months, four visits over the second six months, and three visits over the first six months with an exercise physiologist). In the intensive intervention group, nutrition counselling will be provided using motivational interviewing techniques to encourage quality engagement. Collaborative goal setting will be used to develop personalised nutrition care plans. Individualised advice regarding physical activity will be provided by an exercise physiologist. The primary outcome of the study is weight at six months after transplant, adjusted for baseline (one month post-transplant) weight, obesity and gender. Secondary outcomes will include changes in weight and other anthropometric measures over 12 months, body composition (in vivo neutron activation analysis, total body potassium, dual-energy X-ray absorptiometry, and bioelectrical impedance), biochemistry (fasting glucose, lipids, haemoglobin A1c and insulin), dietary intake and nutritional status, quality of life, and physical function.

**Discussion:**

There are currently few randomised clinical trials of nutrition interventions after kidney transplantation. The INTENT trial will thus provide important data on the effect of intensive nutrition interventions on weight gain after transplant and the associated metabolic consequences. Additionally, by assessing changes in glucose metabolism, the study will also provide data on the feasibility of undertaking larger multi-centre trials of nutrition interventions to reduce the incidence or severity of diabetes after transplantation.

**Trial registration:**

Australian New Zealand Clinical Trials Registry Number: ACTRN12614000155695

## Background

Kidney transplantation represents the optimal form of renal replacement therapy and, compared with dialysis treatment, is associated with significantly improved survival [1, 2], quality of life [3] and reduced costs over time [4, 5]. However, despite improvements in both patient and graft survival, kidney transplant recipients continue to have increased mortality compared with the general population [6]. This is predominantly due to an increased risk of cardiovascular disease [7, 8]. Excessive weight gain, obesity and diabetes are important risk factors for cardiovascular disease in transplant recipients, and are associated in multiple studies with an increased risk of death, cardiac events and graft loss (necessitating a return to dialysis treatment), even when confounding factors are taken into account [9–13].

In the first year following kidney transplantation, there is a significant incidence of excess weight gain and obesity in transplant recipients, with average post-transplant weight gains of 10-35% reported [14–18]. These changes are associated with increased total body fat, reduced lean muscle mass and reduced bone mineral density [17, 19–22]. Excess weight gain in the first year after transplant has also been shown to be a risk factor for the development of metabolic syndrome and new-onset diabetes after transplant (NODAT) [23–27]. Possible causes for weight gain include the use of immunosuppressive medications (such as corticosteroids), the relaxation of dietary restrictions associated with dialysis treatment (increased freedom of food and fluid choices, which may lead to increased energy intake), and improvements in well-being and appetite associated with the resolution of the uraemic state [10, 28–30]. In addition, studies indicate that many transplant recipients do not engage in adequate levels of physical exercise and activity, despite the improvements in overall well-being [31–33].

Despite concern about weight gain and obesity following kidney transplantation, not all post-transplant weight gain is considered undesirable. A high incidence of malnutrition has been reported in patients receiving dialysis therapies [34], even in those with a body mass index (BMI) in the overweight or obese range [35]. Low BMI, malnutrition and low muscle mass have been associated with poor survival after kidney transplantation [36, 37]. It is therefore important to consider not only weight but other markers of nutrition (including evidence for protein-energy wasting and serum albumin) and body composition in the assessment and treatment of kidney transplant recipients.

Importantly, weight gain in the first post-transplant year has been shown to be associated with reduced graft survival [38], and obese individuals have an increased risk of death and graft failure in the first 12 months compared with individuals of normal weight [39]. Weight gain after transplant therefore represents a potentially modifiable risk factor for poor outcomes after transplantation that might be an appropriate target for therapeutic intervention.

There are currently no evidence-based clinical guidelines on specific interventions to prevent or manage excessive weight gain and obesity after transplantation, due to a lack of high quality evidence from randomised controlled trials. On the basis of several non-randomised studies, the Caring for Australasians with Renal Impairment (CARI) guidelines have suggested that kidney transplant recipients be referred to a dietitian for advice to prevent weight gain post-transplant, and that this advice should be reinforced via follow-up assessments on a regular basis [40, 41]. Guidelines from the Kidney Disease: Improving Global Outcomes (KDIGO) initiative and the United Kingdom (UK) Renal Association have suggested that obesity is assessed at each visit and weight management services should be available for patients [42, 43].

In the general population, systematic reviews of randomised studies have shown that interventions addressing nutrition, behaviour and physical activity can be effective in reducing weight in obese patients, although the effects are often not sustained over the long term following the intervention programme [44–46]. Interventions that involve regular review (such as fortnightly during the first three months and continued monitoring for at least 12 months) have shown the greatest benefits [47, 48].

In kidney transplant patients, the few studies that have considered the effects of nutrition and exercise interventions on bodyweight within the 12 months after transplant have had inconsistent results: significantly less weight gain [49], a significant reduction in weight gain from baseline for males [50], or no effect on bodyweight [51]. However, the interpretation of results is limited by the study designs; two studies were non-randomised [49, 50] and one was designed to assess the effects of the intervention on hyperlipidaemia [51].

Overall, there is a need to develop effective interventions to minimise the detrimental effects of weight gain and obesity on long-term kidney transplant outcomes. Randomised controlled trials are needed to assess whether nutrition interventions are likely to be effective in preventing weight gain after kidney transplantation.

The effect of **INTE**nsive **N**utrition interventions on weight gain after kidney **T**ransplantation (INTENT) trial is a randomised controlled trial designed to evaluate the effect of an intensive nutrition intervention, including tailored advice regarding exercise and physical activity, on weight gain in the first year following kidney transplantation. In addition, detailed measures of the effects of the nutrition intervention on other anthropometric measures, body composition, glucose metabolism and biochemical markers of metabolic risk, functional capacity and quality of life will be performed. The trial will also provide data on the feasibility of conducting larger trials of nutrition interventions to reduce the incidence or severity of diabetes after kidney transplantation.

## Methods/Design

### Study aims and hypothesis

The primary aim of the INTENT trial is to determine whether the use of an intensive nutrition intervention, including physical activity advice, following kidney transplantation will be effective at reducing weight gain in the first year post-transplant.

Secondary aims are to determine whether the use of an intensive nutrition intervention will be associated with improvements in anthropometry, body composition, glucose metabolism and markers of metabolic risk; also, whether the use of an intensive nutrition intervention has any effects on dietary intake, nutritional status, quality of life, and physical function.

Our hypothesis is that early intensive nutrition intervention, including advice regarding physical activity, after kidney transplantation will be effective at reducing weight gain in the first post-transplant year, compared with standard post-transplant care.

The INTENT trial will be used to assess the feasibility of undertaking a larger study to determine if nutrition interventions early after kidney transplant can reduce the incidence and severity of diabetes after transplantation (and thus potentially the risk of cardiovascular events). The primary feasibility outcome will be whether a difference in haemoglobin A1c (HbA1c) is observed between the intervention and standard care groups at 12 months.

### Study design

The INTENT trial is a single-centre, single-blind, randomised controlled trial with outcomes assessment blinded to group allocations. An outline of the study is shown in Figure 1.

**Figure 1 Fig1:**
[figure not shown]
**Flowchart of the INTENT trial.**

### Ethical considerations

Ethical approval has been obtained through the Northern B Health and Disability Ethics Committee of the Ministry of Health in New Zealand.

### Target population and eligibility criteria

The target population for the trial will be adult kidney transplant recipients, residing within the Auckland regional area, and recruited during routine post-transplant care within one month of a kidney transplant procedure at Auckland City Hospital.

Inclusion criteria will include the following: age > 18 years; stable graft function, as determined by the patient’s treating physician; willing and able to participate in all trial procedures for the duration of trial follow-up; and ability to provide written informed consent.

Exclusion criteria will include the following: severe obesity, defined by BMI >40 kg/m^2^; underweight, defined by BMI <18.5 kg/m^2^; evidence of significant malnutrition requiring enteral or parenteral nutrition therapy; ongoing significant medical complications that in the opinion of the patient’s treating physician preclude involvement in the trial; and considered likely to become pregnant during the duration of the trial.

Diabetes, cardiovascular disease or other stable medical co-morbidities post-transplant will not be exclusions *per se* unless deemed to represent a contraindication to participating in the trial by the patient’s treating physician. Patients who have been or are receiving treatment for acute rejection will not be excluded, providing graft function is stable at the time of entry to the trial in the opinion of the patient’s treating physician. Participation in another clinical trial will not be an exclusion providing that such participation will not compromise involvement in this trial, in the opinion of the principal investigator.

### Recruitment, randomisation and blinding

Potential participants will be identified during their initial inpatient stay following transplantation at Auckland City Hospital, or through the renal transplant outpatient clinic following discharge. Eligible transplant recipients will be invited to participate, given detailed information about the trial and, if agreeable, will be asked to provide written informed consent. In order to participate, transplant recipients will need to provide informed consent and be randomised prior to one month post kidney transplantation.

Participants will be randomised in a 1:1 ratio to receive either intensive nutrition intervention or standard of care. Randomisation will be performed externally by a statistical consultant using a computer-generated sequence allocation with permuted blocks of variable size, and stratified by gender. Allocation concealment will be via sealed opaque envelopes.

Formal study assessments of weight, anthropometry, measures of body composition, and physical function will be performed by one of the investigators, who will be blinded to the group allocation of participants. Laboratory staff blinded to the group allocations will perform all laboratory testing.

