### Intensive nutrition intervention group

Patients randomised to the intensive nutrition intervention group will, in addition to standard care, receive more frequent counselling with a specialist renal dietitian throughout the trial. These will commence at one month post-transplant and include an additional 8 visits overall compared to the standard care group (see Table 1). Participants will also receive individualised assessment and advice regarding physical activity and exercise, via formal consultations with an exercise physiologist at 2 months, 3 months and 6 months post-transplant.

**Table 1 Tab1:** **Schedule of nutrition assessment**, **education and advice provided by renal dietitian and exercise physiologist** (**intensive nutrition intervention group**)

**Months 1** **-** **3**	**Fortnightly** review with dietitian to undertake initial assessments, determine progress, goals and adherence to recommendations
	Full review of dietary intake and adequacy of adherence to recommendations to be undertaken at 1 month and 3 months (including 3-day food diary and analysis)
	Exercise advice (including a consultation with an exercise physiologist at 8 and 12 weeks to provide tailored advice) regarding physical activity and a review of physical activity adherence
**Months 4** **-** **6**	**Monthly** review with dietitian to assess progress, goals and adherence to recommendations, and give further education and advice as appropriate
	Full review of dietary intake and adequacy of adherence to recommendations to be undertaken at 6 months (including 3-day food diary and analysis)
	Exercise advice (including a consultation with an exercise physiologist at 6 months to provide tailored advice) regarding physical activity and a review of physical activity adherence
**Months 7** **-** **12**	**Bi** **-** **monthly** review with dietitian to assess progress, goals and adherence to recommendations, and give further education and advice as appropriate
	A final review of diet history and adequacy of adherence to recommendations to be undertaken at 12 months (including 3-day food diary and analysis)
	Exercise advice to promote adequate physical activity and review of physical activity adherence

Individualised nutrition counselling will be provided using motivational interviewing techniques to encourage quality engagement. Personal nutrition plans will be developed using S.M.A.R.T. action steps, i.e. specific, measureable, achievable, relevant and time-limited [55].

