Prior to full reviews at 1, 3, 6 and 12 months, a self-administered 3-day food diary record will be completed by participants and analysed using appropriate analysis software (e.g. FoodWorks® Professional [Xyris software]). Dietary intake data will be compared to evidence-based recommendations on nutrient requirements after renal transplant and used to guide nutrition prescriptions. At follow-up reviews, renal dietitians will assess progress, goal setting and adherence to dietary recommendations. Adherence will be measured using rulers to assess motivation to change, level of achievement of patient-centred goals and review of action steps taken in patient action plans.

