### Primary and secondary outcomes

The primary outcome will be body weight at 6 months post-transplant, adjusted for weight at baseline (one month post-transplant), pre-existing obesity (BMI ≥30 kg/m^2^), and gender.

Secondary outcomes will include the following: change in weight and other anthropometric measures at 3, 6 and 12 months post-transplant; change in gold-standard body composition parameters post-transplant; validity of bio-electrical impedance assessment as compared with gold-standard body composition analysis in kidney transplant recipients; change in biochemical measures post-transplant (e.g. lipid profile and markers of insulin resistance); adherence to dietary advice in the intervention group; level of physical activity and physical functional capacity in transplant recipients; and quality of life in transplant recipients. In addition, a cost-effectiveness analysis of intensive nutrition intervention will be undertaken taking into account the costs of additional dietitian input (including missed visits), changes in weight and quality of life.

In order to determine the feasibility of undertaking larger multi-centre trials of nutrition interventions to reduce the incidence or severity of diabetes after transplantation, the difference in HbA1c observed between the intervention and standard care groups at 12 months will be reported as an exploratory feasibility outcome.

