### Data collection

Standard demographic, clinical and laboratory data (including medication details) will be collected at baseline (1 month) and at 3, 6 and 12 months post-transplant. This will include details of any acute medical issues, clinical or other adverse events, graft function, acute rejection, hospital admissions, development of diabetes, or any other issues that might affect nutritional status or change in weight. Formal study assessments (blinded to group allocation) will be undertaken at baseline (1 month), and at 3, 6 and 12 months (Table 2).

**Table 2 Tab2:** **INTENT study data collection at baseline and months 3**, **6 and 12 post**-**transplant in the intervention and standard care groups**

Type of data	Specific measure
**Demographics**	Age
	Gender
**Clinical status**	Acute medical issues (including acute rejection, hospital admissions, diabetes status)
	Graft function
**Anthropometry**	Body weight
	Body mass index
	Waist circumference & waist-hip ratio
	Mid-arm circumference
	Skin-fold thickness
**Body composition**	Bioimpedance assessment
	Deuterium dilution (total body water, fat mass)
	DEXA (bone mass and fat mass)
	*In vivo* neutron activation analysis of body nitrogen (total body protein)
	Total body potassium (body cell mass)
**Biochemistry**	Serum creatinine
	Estimated GFR
	Immunosuppression drug levels
	Fasting glucose
	Insulin
	HbA1c
	Total, LDL & HDL cholesterol and triglycerides
	Insulin resistance (HOMA)
**Dietary***	3-day food diary
	Motivational assessment rulers to assess motivation to change
**Physical function**	Gait speed assessment
	Hand grip strength
	Sit-to-stand-to-sit test
**Other**	PG-SGA
	NZPAQ-SF
	SF-36
	Blood pressure

*Only collected for intensive arm.

DEXA = Dual-energy x-ray absorptiometry; GFR = Glomerular filtration rate; HbA1c = Haemoglobin A1c; HDL = High density lipoprotein; LDL = Low density lipoprotein; NZPAQ-SF = New Zealand physical activity questionnaire – short form; PG-SGA = Patient-generated subjective global assessment; SF-36 = Short Form-36.

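### Randomisation is set before one month but the ANCOVA baseline weight is taken at one month, so the key covariate follows unblinded allocation; the bias is probably small and cheap to remove

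*Protocol article*

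**What the plan says.** **Timing of allocation.** Under Recruitment, randomisation and blinding, it is a condition of entry that "transplant recipients will need to provide informed consent and be randomised prior to one month post kidney transplantation". The abstract agrees: "Participants will be randomised during the first post-transplant month". Recruitment may begin during the inpatient stay or later at the outpatient clinic.

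**Timing of baseline.** Under Primary and secondary outcomes, six-month weight is to be "adjusted for weight at baseline (one month post-transplant), pre-existing obesity" and gender. Under Data collection: "Formal study assessments (blinded to group allocation) will be undertaken at baseline (1 month), and at 3, 6 and 12 months". Statistical analysis puts baseline weight and baseline obesity into the ANCOVA and starts the repeated-measures models at the same visit.

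**What happens around one month.** On the intensive dietitian visits: "These will commence at one month post-transplant and include an additional 8 visits overall compared to the standard care group". The same section adds: "Prior to full reviews at 1, 3, 6 and 12 months, a self-administered 3-day food diary record will be completed by participants". The footnote to Table 2 restricts the dietary data to the intensive arm.

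**Blinding.** The outcome assessor is blinded. The Discussion accepts that participants and intervention staff cannot be.

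**The concern.** ANCOVA on a baseline measured before allocation is protected by randomisation, because the arms can differ on it only by chance. That protection weakens once the baseline is measured after people know their arm. Participants told that they will have intensive nutrition support may change how they eat before the one-month weighing, and keeping a three-day food record in one arm only could add to this. Blinding the assessor protects the reading on the scale but not what participants ate beforehand.

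Part of the effect would then sit in the covariate and be adjusted out of the primary estimate. Secondary changes from baseline would start from the same point, and the self-reported baselines (SF-36, NZPAQ-SF) would be completed by people who may know their allocation. The analysis cannot reliably undo this unless a usable pre-allocation weight was also recorded. The trial needs 28 participants and aims for at most 32, so it has little power to spare.

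**Working it through.** **Inputs from Calculation of required sample size.** Difference 5 kg; SDs 9 and 12 kg; correlation between baseline and six-month weight 0.9; power 80%; alpha 5% (taken as two-sided); 14 per group.

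**Step 1: reproduce the planned figure.**

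n per group = (SD1² + SD2²)(z0.975 + z0.80)² / δ² × (1 − r²)

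= (81 + 144) × 7.849 / 25 × (1 − 0.81) = 70.64 × 0.19 = 13.42, rounded up to 14.

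This matches the protocol, so the sample-size arithmetic is not at fault. A one-sided test would give 11, and the observed correlation of 0.9514 would give 7, so the plan's figure is two-sided with r = 0.9.

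**Step 2: power as planned.** Pooled SD = √(225/2) = 10.61 kg. Residual SD = 10.61 × √0.19 = 4.62 kg. Standard error at 14 per group = 4.62 × √(2/14) = 1.75 kg. Power = Φ(5/1.75 − 1.96) = 81.6% (normal approximation).

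**Step 3: effect of an arm difference already present at baseline.** If the arms differ by g kg at the one-month weighing because of allocation, ANCOVA estimates

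5 − b × g, with b = r × (SD at 6 months / SD at baseline).

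Taking equal SDs at the two times (an assumption), b = 0.9.

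**Step 4: range for g.** The documents give no value, so g is an assumption.

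| Assumed g (kg) | Removed, 0.9 × g (kg) | Share of 5 kg | Estimate (kg) | Power at 14 per group | n per group for 80% |
|---|---|---|---|---|---|
| 0 | 0 | 0% | 5.00 | 81.6% | 14 |
| 0.25 | 0.225 | 4.5% | 4.78 | 78.0% | 15 |
| 0.5 | 0.45 | 9% | 4.55 | 74.0% | 17 |

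**Step 5: check of the formula.** In 4,000 simulated trials of 14 per group with a true effect of 5 kg, the mean ANCOVA estimate was −5.02 kg with no shift. With a 1 kg shift, used only to test the formula, it was −4.09 kg, against −4.10 kg predicted.

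**Step 6: how large could g be?** The planned 5 kg arises between months 1 and 6, which is 5/5 = 1 kg per month for the full programme. The mean gain in the local cohort over those months was 3.2 kg, or 3.2/5 = 0.64 kg per month. A shift of 1 kg within at most about four weeks, before any intensive counselling, would mean that knowing one's allocation works as fast as the whole programme is assumed to. A range of 0.25 to 0.5 kg is a more cautious illustration, and the true value may be nearer zero.

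**The case against.** The best case for the plan is that almost nothing differs between the arms before the baseline visit. Intensive visits start at one month. Until then both arms have the same inpatient dietitian assessment, and standard care also includes a one-month consultation. What remains is knowledge of allocation and one short diary, over a window that is shorter still for people recruited as outpatients. If neither moves weight, the ANCOVA is valid as written. The likely direction is also conservative: early restraint in the intensive arm shrinks the estimate and does not manufacture an effect. Finally, the flowchart is not visible, and no text gives the day-by-day order of envelope, weighing and first visit.

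Most of this stands, and it limits the size of the point. It does not remove the stated ordering, under which allocation comes before one month and baseline at one month. Nor does any text put the weighing ahead of the first intensive contact.

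Some stronger readings do not hold:

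- **A 1 kg divergence**, costing 18% of the effect and taking power to 65.0%. Nothing in the documents supports a shift that large before counselling begins.
- **Setting the loss against the 3.2 kg gain.** That figure is a cohort's mean weight change and not a treatment effect; only the 5 kg contrast is relevant.
- **Treating the obesity covariate as certainly post-allocation.** Primary and secondary outcomes calls it pre-existing, Statistical analysis calls it baseline, and the eligibility limits already need a BMI. Which BMI is used is not fixed.
- **Counting losses between allocation and one month as a demonstrated harm.** This is possible but speculative, and the handling of missing data may be set out in a plan not shown.

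**Conclusion.** The point holds as a design weakness of modest size. The stated timings place the primary covariate, and the origin of the change and mixed-model analyses, after allocation in unblinded participants. Each kilogram of arm difference already present at one month costs about 0.9 kg of the estimated effect, assuming r = 0.9 and equal SDs.

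With an assumed shift of 0.25 to 0.5 kg, about 0.2 to 0.45 kg of the planned 5 kg is lost (5 to 9%), and power falls from about 82% to 78 to 74%. The bias runs mainly towards no effect; it would reverse only if controls were the ones to lose weight early. A reader might infer that the primary analysis is invalid or that a large part of the effect will be lost. The documents do not support that. The ordering is well supported, but a material bias is not shown. The change is recommended because it is cheap and the problem is hard to repair afterwards; it is not a condition for the trial to proceed.

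**What to change.** Keep consent within the first month. Replace the requirement to randomise before one month with randomisation at the one-month baseline visit: the envelope is opened after weight, BMI, body composition, bloods and questionnaires are complete, and before any intensive-arm contact. Someone other than the blinded assessor should open it. Align the sentence in the abstract, and state that the obesity covariate comes from a BMI recorded before allocation.

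The cost is one protocol sentence, with its echo in the abstract, and some scheduling. Intensive visits already start at one month, so little intervention time is at risk, but there are two downsides. The first intensive visit must be booked at short notice. The first food diary, if it stays confined to the intensive arm, has to follow allocation, which delays the first full dietary review by a few days. Asking everyone to keep the diary before allocation would avoid the delay, but would give controls a self-monitoring task that the design leaves out.
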